#### Safety

- To examine the occurrence of adverse events related to the use of a personalized hemodynamic resuscitation protocol within 48 hours and 7 days.
- To assess the rate of acute kidney injury associated with the use of a personalized hemodynamic resuscitation protocol within 48 hours and 7 days.

### Health technology:

- To compare the cost-effectiveness when using the personalized hemodynamic protocol guided by Starling SV monitor versus standard protocols at the emergency department (ED).

#### Exploratory mechanistic endpoints:

- To explore the inter-individual differences in hemodynamic endotypes between sepsis patients at the emergency department (ED).
- To compare the accuracy of the Starling SV monitor with other diagnostic tools such as PoCUS at triage in diagnosing fluid responsiveness in sepsis patients.
- To explore other diagnostic tools in the stratification of hemodynamic endotypes between sepsis patients.

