#### Groups

Experimental arm: personalized hemodynamic resuscitation (94 patients)

Patients will receive an IV fluid bolus directly after inclusion. Next, measurement of the stroke volume index change in response to the fluid bolus by the Starling SV will be used to determine fluid responsiveness. Vital parameters and fluid responsiveness will be used to guide hemodynamic resuscitation, consisting of IV fluids and/or vasopressors, during the first 3 hours. See chapter 5 and figure 1 for a detailed description of the study procedures.

Control arm: standard care (94 patients)

Patients will receive an IV fluid bolus directly after inclusion. Vital parameters will be used to guide hemodynamic resuscitation, consisting of IV fluids and/or vasopressors, during the first 3 hours. See chapter 5 for a detailed description of the study procedures.

[figure not shown]

**Figure 1: Flowchart personalized protocol.** Adult patients with confirmed or suspected infection with need for hemodynamic resuscitation, will be included into the study. A dynamic assessment of fluid responsiveness using the Starling SV monitor will be performed at every clinical decision point with concordant treatment (volume or vasopressors). MAP: mean arterial pressure; SBP: systolic blood pressure; NE: noradrenaline; PoCUS: Point-of-Care Ultrasound; L: lactate; SI: shock index\*; CI: cardiac index; PLR: passive leg raise; IV: intravenous; \*shock index is heart rate divided by systolic blood pressure;

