## 5. TREATMENT OF SUBJECTS

### 5.1 Investigational product/treatment

#### Intervention:

The investigational product in this study is the Starling SV monitor, which is a medical device manufactured by Baxter Healthcare. The Starling SV monitor is a non-invasive hemodynamic monitor that provides real-time continuous information about stroke volume index, cardiac index, cardiac output, and total peripheral resistance. In this intervention study, the Starling SV monitor is designed to assist in guiding hemodynamic resuscitation for patients with sepsis.

In the experimental group, patients will receive hemodynamic resuscitation guided by the Starling SV monitor. A dynamic assessment of fluid responsiveness using the monitor will be performed at every clinical decision point during the first three hours of study enrolment.

Vital parameters, including blood pressure and heart rate, are measured upon ED arrival (triage), immediately after administration of a fluid bolus and at least twice per hour during the first 3 hours. Lactate will be measured at ED arrival (triage) and will be repeated every two hours as long as lactate is  $> 4$  mmol/L. Fluid responsiveness will be measured by the Starling SV monitor immediately before and after the administration of fluids. Fluid responsiveness is defined as an increase in stroke volume index by at least 10% after a fluid bolus of 500 mL in 10 min.

First, we will perform the first measurement during the first administration of 500 mL of IV fluids. During both the fluid bolus, we will measure the change in stroke volume index ( $\Delta$ SVI) using the Starling SV and use the stroke volume index change in response to the fluid bolus to determine fluid responsiveness.

If, at any time during the first 3 hours, patients have: (see figure 1)

- MAP  $< 65$  mmHg or systolic blood pressure  $< 90$  mmHg:
  - Fluid responsive (on last measurement): patients will receive (another) 500 mL of IV fluids if considered fluid responsive (and a new Starling SV measurement will be obtained). Reassess after intervention.
  - Not fluid responsive (on last measurement): patients will receive vasopressor (noradrenaline), according to the standard care protocol.\*
- MAP  $\geq 65$  mmHg or systolic blood pressure  $\geq 90$  mmHg combined with SI  $> 0.9$ :

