**Exploratory mechanistic endpoints**

|                      |                                                                                                                                                                                                                                                                                                                                                                                                                                                                                                                                                                         |
|----------------------|-------------------------------------------------------------------------------------------------------------------------------------------------------------------------------------------------------------------------------------------------------------------------------------------------------------------------------------------------------------------------------------------------------------------------------------------------------------------------------------------------------------------------------------------------------------------------|
| Hemodynamic endotype | 
 
• Starling SV monitor parameters (e.g. CI, TPRI, SVI) up to three hours after ED arrival
 
• Hemodynamic parameters (e.g. systolic blood pressure, diastolic blood pressure, MAP, heart rate, lactate, CRT) up to three hours after ED arrival
 
• Photoplethysmography waveform characteristics (e.g. systolic and diastolic peak amplitude) during ED stay
 
• Electrocardiography waveform characteristics (e.g. pulse-transit-time and heart rate variability (HRV)-features) during ED stay
 
 |
|----------------------|-------------------------------------------------------------------------------------------------------------------------------------------------------------------------------------------------------------------------------------------------------------------------------------------------------------------------------------------------------------------------------------------------------------------------------------------------------------------------------------------------------------------------------------------------------------------------|

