**Fluid responsiveness assessment procedure**

A dynamic assessment of fluid responsiveness using the Starling SV monitor will be performed at every clinical decision point for the first three hours of study enrollment. (*see figure 1 'flowchart personalized protocol'*). Fluid responsiveness will be assessed in response to an IV fluid bolus of 500 mL in 10 min using the Starling SV hemodynamic monitor. To guide hemodynamic resuscitation, fluid responsiveness will be defined based on an increase in stroke volume in response to the fluid bolus.

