| Vasopressor therapy (time, amount, type)                                                                               |               | x               | x                | x          |           |            |
| (Elektro)physiological waveform data: (e.g.. PPG, ECG)                                                                 |               | x               |                  |            |           |            |
| PoCUS data (e.g. IVC diameter, collapsibility index, lung US)                                                          |               | x               | x                |            |           |            |
| Pre-tibial edema score                                                                                                 |               | x               | x                | x          |           |            |
| Cost-effectiveness data (i.e. costs and wins)                                                                          |               | x               |                  |            |           | x          |

**Table 1: description and timeline of data collection** \* Screening and ED visit occur on the same day. \*\* Follow up of severity scores is up to 7 days (or hospital ward discharge, whichever came first); hospital ward discharge comprises admission to the ICU or discharge home.

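### The exploratory aim of comparing the monitor's accuracy with ultrasound has no reference standard other than the monitor itself, so the plan supports a statement of agreement but not an accuracy ranking

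*Protocol*

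**What the plan says.** Section 2 of the protocol, under the exploratory mechanistic endpoints, sets this aim: "To compare the accuracy of the Starling SV monitor with other diagnostic tools such as PoCUS at triage in diagnosing fluid responsiveness". It names no reference standard.

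Three places say how responsiveness is established, and all three use the monitor:

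- Section 3, Groups: "measurement of the stroke volume index change in response to the fluid bolus by the Starling SV will be used to determine fluid responsiveness".
- Section 5.1, Intervention: "Fluid responsiveness will be measured by the Starling SV monitor immediately before and after the administration of fluids", followed by "Fluid responsiveness is defined as an increase in stroke volume index by at least 10" per cent, after a bolus of 500 mL in 10 minutes.
- Section 8.3, fluid responsiveness assessment procedure: "Fluid responsiveness will be assessed in response to an IV fluid bolus of 500 mL in 10 min using the Starling SV hemodynamic monitor".

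Two places list the data that could bear on the comparison:

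- Table 1 in section 8.3 has a row beginning "PoCUS data (e.g. IVC diameter, collapsibility index, lung US". It is marked at 0h and 24h and has no mark under Triage.
- The exploratory endpoint table in section 8.1.2 has one entry, hemodynamic endotype. It covers "Starling SV monitor parameters (e.g. CI, TPRI, SVI) up to three hours after ED arrival", other hemodynamic parameters, and photoplethysmography and electrocardiography waveforms. It contains no accuracy endpoint.

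Thermodilution and the pulmonary artery catheter appear only in section 6.3, as part of earlier validation work.

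**The concern.** Comparing the accuracy of two diagnostic tools requires a third source that settles the true state of each patient. In this protocol the only stated source is one of the two tools. When the index test also supplies the reference, the comparison has incorporation bias: the monitor's errors cannot show up as monitor errors and are counted against the comparator.

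At stake is a claim that the monitor diagnoses fluid responsiveness more accurately than ultrasound, which these data could not establish. The protocol itself lists inaccurate readings among the monitor's risks (sections 10.4 and 12.2), so an error-free monitor cannot be taken for granted. The choice of accuracy metric can wait for the statistical analysis plan. A reference measurement cannot, because an analysis plan cannot supply a measurement that the protocol does not name.

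**Working it through.** The protocol gives no sensitivity, specificity or accuracy figure, so there is nothing to reproduce. The check is logical, followed by an illustration on assumed error rates.

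**Step 1: the identity.** Let S be the monitor's classification (stroke volume index rise of at least 10% after the bolus: yes or no). Let R be the reference. Sections 3, 5.1 and 8.3 give only R = S. If the monitor's index test is the same bolus reading, then

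accuracy of monitor = P(S = R) = P(S = S) = 100%.

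Sensitivity and specificity are 100% for the same reason, whatever the monitor's real error. A comparator C scores P(C = S), which cannot exceed 100%. It can tie, but it cannot win.

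**Step 2: what a comparator would score.** Let T be the true state, m the monitor's true misclassification rate and a the comparator's true accuracy. Neither m nor a is in the protocol; both are assumed. If the two tools err independently,

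P(C = S) = a(1 − m) + (1 − a)m.

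For a perfect comparator (a = 1) this reduces to 1 − m, and independence is not needed.

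| Assumed m | Monitor against itself | Perfect comparator | Comparator truly 95% | Comparator truly 80% |
|---|---|---|---|---|
| 10% | 100% | 90% | 0.95×0.90 + 0.05×0.10 = 86% | 0.80×0.90 + 0.20×0.10 = 74% |
| 20% | 100% | 80% | 0.95×0.80 + 0.05×0.20 = 77% | 0.80×0.80 + 0.20×0.20 = 68% |
| 30% | 100% | 70% | 0.95×0.70 + 0.05×0.30 = 68% | 0.80×0.70 + 0.20×0.30 = 62% |

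In the last row the comparator with 80% true accuracy beats the monitor's 70%, yet it would be reported as 62% against 100%.

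**Step 3: simulation with continuous measurement error.** Assumptions: true percentage change in stroke volume index normal with mean 10 and SD 12; monitor error SD of 0, 5, 10 or 15 points; 400,000 simulated patients.

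| Error SD (points) | Monitor against itself | Monitor against truth | 95% comparator against monitor | 80% comparator against monitor |
|---|---|---|---|---|
| 0 | 100% | 100% | 95% | 80% |
| 5 | 100% | 87.3% | 83.6% | 72.4% |
| 10 | 100% | 77.8% | 75.0% | 66.7% |
| 15 | 100% | 71.4% | 69.2% | 62.8% |

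The formula in step 2 agrees with the simulation. At error SD 15, m = 1 − 0.714 = 0.286, and 0.80×0.714 + 0.20×0.286 = 62.8%.

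**Step 4: a different index from the same monitor.** Suppose the monitor's test were a passive leg raise response or stroke volume variation, judged against the later bolus reading. The identity in step 1 no longer holds, so the score need not be 100%. The same device still produces both test and reference, so error that persists within the device in a given patient raises their agreement and does nothing for ultrasound. The bias still favours the monitor, but its size cannot be derived from the protocol.

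**The case against.** The strongest objection is that the definition in section 5.1 is a working rule for treating patients, and section 8.3 ties it to guiding resuscitation. The protocol never says that this rule is the reference for the diagnostic comparison. For an exploratory aim, an analysis plan that is not shown here might set the reference. This stands in part: the equation of rule and reference is inferred. It is nonetheless the only definition of the target condition in the document, and no other measurement that could serve as a reference is named.

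A reader might also infer stronger conclusions, which the document does not support:

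- **That the monitor's accuracy is 100% without condition.** This needs the index test to be the same bolus reading. Passive leg raise appears in the legend of Figure 1 (the figure itself is not shown), and section 6.1 lists stroke volume variation and posture-related changes among the monitor's outputs.
- **That any other tool must look worse, or that the trial must declare the monitor superior.** A comparator that agrees in every patient ties.
- **That no independent reference is collected.** The PoCUS row in Table 1 is an open list of examples. The supportable statement is that none is named.

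Finally, every misclassification rate used above is assumed. The figures show the direction of the bias and how it grows with monitor error; they do not estimate what this trial would find.

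**Conclusion.** The point holds in a limited form. As written, the objective asks for an accuracy comparison in which one of the compared tools supplies the only stated definition of the condition. With the bolus reading as index test, the result is fixed at 100% for the monitor and at most 100% for anything else. With another index from the same monitor, the comparison is biased in the same direction by an unknown amount. Under assumed monitor misclassification of 10% to 30%, a perfect comparator would appear 90% to 70% accurate.

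The data described can support agreement of other tools with monitor-defined responsiveness. They cannot rank the tools by accuracy. The primary endpoint and the sample size do not depend on this, so it is a minor point on an exploratory objective.

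**What to change.** Reword the objective in section 2 as: *To assess the agreement of PoCUS and other tools with monitor-defined fluid responsiveness.* Report agreement, for example kappa for a dichotomised ultrasound finding, or the AUC of the ultrasound measure against the monitor-defined response. Make no claim about the monitor's relative accuracy unless an independent reference standard is named in the protocol.

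In the same edit, reconcile the PoCUS timing between the objective (triage) and Table 1 (0h and 24h, nothing under Triage), so that it is clear which scan enters the comparison.

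The cost is one reworded sentence and one timing correction. Nothing the planned data could support is lost; only an accuracy ranking is given up. Keeping the accuracy aim instead would cost more, because it would need an additional reference measurement.

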### 3. STUDY DESIGN

#### Study design

This is a **randomized open clinical trial**. Patients will be recruited by the FLUIDS-team of researchers in the emergency department (ED) of the University Medical Centre Groningen (UMCG). The ED physician and/or nurse will screen all patients entering the ED for inclusion in the current study (on weekdays, between 9 am - 5 pm). The FLUIDS-team of researchers will subsequently enroll eligible patients in the study protocol. To ensure timely intervention in the acute setting and limit selection bias, we use deferred consent (by proxy).

#### Strategy/setting

Adult patients with a suspected infection at the ED (*see section 'key inclusion criteria' for definition*) and able to maintain a supine position, will be recruited. In this study, we will compare the Starling SV monitor as guide for hemodynamic resuscitation (intervention) vs standard care. Patients are assigned randomly. Randomization is in a 1:1 allocation of SVI-guided to standard care. All fluids administered will be balanced fluids.

#### Duration

The clinical trial is expected to span 12 months. The trial will involve a total of 188 patients. We conducted a preliminary assessment of the inclusion rate in our emergency department and identified an average of four patients per week meeting the study's criteria for inclusion.

#### Groups

Experimental arm: personalized hemodynamic resuscitation (94 patients)

Patients will receive an IV fluid bolus directly after inclusion. Next, measurement of the stroke volume index change in response to the fluid bolus by the Starling SV will be used to determine fluid responsiveness. Vital parameters and fluid responsiveness will be used to guide hemodynamic resuscitation, consisting of IV fluids and/or vasopressors, during the first 3 hours. See chapter 5 and figure 1 for a detailed description of the study procedures.

Control arm: standard care (94 patients)

Patients will receive an IV fluid bolus directly after inclusion. Vital parameters will be used to guide hemodynamic resuscitation, consisting of IV fluids and/or vasopressors, during the first 3 hours. See chapter 5 for a detailed description of the study procedures.

[figure not shown]

**Figure 1: Flowchart personalized protocol.** Adult patients with confirmed or suspected infection with need for hemodynamic resuscitation, will be included into the study. A dynamic assessment of fluid responsiveness using the Starling SV monitor will be performed at every clinical decision point with concordant treatment (volume or vasopressors). MAP: mean arterial pressure; SBP: systolic blood pressure; NE: noradrenaline; PoCUS: Point-of-Care Ultrasound; L: lactate; SI: shock index\*; CI: cardiac index; PLR: passive leg raise; IV: intravenous; \*shock index is heart rate divided by systolic blood pressure;

## 4. STUDY POPULATION

### 4.1 Population (base)

Subjects will be enrolled upon Emergency Department (ED) arrival. Adult patients with confirmed or suspected infection with a need for hemodynamic resuscitation will be considered a candidate for the study. A subject needs to be enrolled within one hour after ED arrival. Once enrolled, subjects will be randomly assigned using the designated randomization procedure. After confirming that the inclusion and exclusion criteria are met, the Starling sensors will be positioned and connected to the Starling SV monitor. To ensure accurate data collection during the study, the readings from the sensors will be validated before initiating the data collection period. To ensure timely intervention in this acute setting, a deferred consent (DC) strategy is employed, facilitated by a proxy if necessary. More information about the DC-procedure is available in 'Chapter 11.2: Recruitment and consent'.

### 4.2 Inclusion criteria

In order to be eligible to participate in this study, a subject must meet all of the following criteria:

- Adult patients ( $\geq 18$  years of age);
- Referred to internal medicine, nephrology, geriatric medicine, oncology, hematology, lung medicine, rheumatology, gastrointestinal / liver medicine, urology, or emergency medicine (non-trauma);
- Confirmed or suspected infection according to the physician's judgement upon arrival to the ED, based the presence of an acute phase response not due to an alternative non-infectious cause (i.e., body temperature  $< 36^{\circ}\text{C}$  or  $> 38^{\circ}\text{C}$ , leukocyte count  $> 12 \times 10^9/\text{L}$  or C-reactive protein  $> 50 \text{ mg/L}$ ), and/or on symptoms suggestive for an infection (e.g. productive cough, dyspnea, dysuria, pollakisuria, abdominal pain, erythema)
- Need for hemodynamic resuscitation, based on any of the following (*first measurement at ED arrival [triage]*):
  - Mean arterial pressure (MAP)  $< 70 \text{ mmHg}$
  - Systolic blood pressure (SBP)  $< 90 \text{ mmHg}$  or a SBP decrease  $> 40 \text{ mmHg}$
  - Lactate  $> 4.0 \text{ mmol/L}$
  - Shock index\*  $> 0.9$
- Enrolled in study within one hour after ED arrival

\* Shock index is the heart rate divided by the systolic blood pressure, an indicator for the severity of hypovolemic shock.

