  - Fluid responsive (on last measurement): patients will receive (another) 500 mL of IV fluids if considered fluid responsive (and a new Starling SV measurement will be obtained). Reassess after intervention.
  - Not fluid responsive (on last measurement): repeat measurement in 30 minutes.
    - If (MAP  $\geq 65$  mmHg and systolic blood pressure  $\geq 90$  mmHg) combined with SI  $> 0.9$ : optional 500 mL of IV fluids based on rescue rules. Reassess after intervention;
    - If MAP  $< 65$  mmHg or systolic blood pressure  $< 90$  mmHg: see above;
    - If (MAP  $\geq 65$  mmHg and systolic blood pressure  $\geq 90$  mmHg) combined with SI  $\leq 0.9$ : see below.
- MAP  $\geq 65$  mmHg and systolic blood pressure  $\geq 90$  mmHg, combined with SI  $\leq 0.9$ : no action needed.

Rescue fluids (500 mL of IV fluids) recommended if, at any time during the first 3 hours, patients have any of the following conditions:

- Severe hypotension (systolic blood pressure  $< 70$  mmHg or MAP  $< 50$  mmHg)

- Refractory hypotension (systolic blood pressure < 90 mmHg or MAP < 65 mmHg) with administration of noradrenaline at dose of 20 mcg/min or of an equivalent dose of another vasopressor)
- Lactate level > 4 mmol/liter and increasing after 2 h of therapy
- Sinus heart rate > 130 beats/min for > 15 min
- PoCUS evidence of extreme hypovolemia

All fluids administered will be balanced fluids. In addition to the fluid resuscitation as described above, all patients will receive a standard 1.5 L per day of IV fluids from the moment of ED arrival. The total volume of IV fluids will be limited to a maximum of 60 ml/kg over three hours to prevent hypervolemia.

\* Vasopressor therapy initiated according to personalized protocol will be performed in the stepwise approach of standard care. Every 30 minutes vital parameters will be repeated. According to the protocol it can be that vasopressor therapy needs to be increased or that fluids will be administered, as vasopressors can cause fluid responsiveness due to increased venous return.

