| Hemodynamic resuscitation | 
 
Time to recovery of normal perfusion/hemodynamic stability (HDS)*
 
Proportion of patients reaching normal perfusion/hemodynamic stability* within three hours
 
                                                                                                                                                                       |

\* Hemodynamic stability (HSD) is defined as MAP  $\geq$  70 mmHg. SBP  $\geq$  90 mmHg, lactate  $\leq$  4 mmol/L and SI  $\leq$  0.9.

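### A patient who enters only on an SBP fall of more than 40 mmHg already meets the hemodynamic stability definition at triage, which dilutes both stability endpoints

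*Protocol*

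**What the plan says.** Section 4.2 lists "Need for hemodynamic resuscitation, based on any of the following", scored on the first reading at ED arrival. The items are MAP below 70 mmHg, SBP below 90 mmHg "or a SBP decrease" of more than 40 mmHg, lactate above 4.0 mmol/L, and shock index (SI) above 0.9. No usual, pre-hospital or earlier pressure is named as the comparator. Table 1 lists vital parameters from triage onward and no reference SBP.

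The footnote to the efficacy table in section 8.1.2 says "Hemodynamic stability (HSD) is defined as MAP" of at least 70 mmHg, SBP of at least 90 mmHg, lactate of at most 4 mmol/L and SI of at most 0.9. Two secondary endpoints use it: the time to recovery of HDS, and the "Proportion of patients reaching normal perfusion/hemodynamic stability" within three hours. No rule covers patients who meet the definition at entry.

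On treatment, section 3 says for each arm: "Patients will receive an IV fluid bolus directly after inclusion". In the guided arm, section 5.1 then gives "no action needed" when MAP is at least 65 mmHg, SBP at least 90 mmHg and SI at most 0.9.

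**The concern.** An endpoint that measures recovery needs patients who have something to recover from. Four of the five entry conditions guarantee this, because meeting any of them means failing HDS. The SBP fall does not. Patients who enter on it alone are successes at time zero whatever their arm. They carry no treatment contrast on either HDS endpoint and pull both comparisons toward no difference.

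Section 1 expects the guided strategy to shorten the time to hemodynamic stability, and these two endpoints are where that would be seen. The unnamed comparator adds a smaller problem. Two enrollers could score the same patient differently, and the basis for entry could not be checked afterwards from the data listed in Table 1.

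**Working it through.** **The plan's own figure.** The only stated sample size is for the primary endpoint (section 4.4): means 0.65 and 2.02 L, SDs 2.85 and 3.44 L, two-sided Welch test at 0.05. The difference is 1.37 L and the root-mean-square SD is √((2.85² + 3.44²)/2) = 3.159 L. Welch power at 85 per arm is 80.3%, against 79.8% at 84, so 170 is reproduced. Adding 10% per arm gives 85 × 1.10 = 93.5, rounded to 94, or 188 in total. None of this depends on HDS. The protocol gives no HDS rate, effect or power.

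**Entry and HDS side by side.**

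| Entry (any one) | HDS (all) |
|---|---|
| MAP < 70 mmHg | MAP ≥ 70 mmHg |
| SBP < 90 mmHg | SBP ≥ 90 mmHg |
| SBP decrease > 40 mmHg | none |
| Lactate > 4.0 mmol/L | Lactate ≤ 4 mmol/L |
| SI > 0.9 | SI ≤ 0.9 |

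Failing the four paired entry items is the same as meeting HDS. So a patient who qualifies on the fall alone meets HDS at triage, and no other route allows this at that reading.

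**Example (assumed values).** Usual SBP 160, triage 115/70, heart rate 80, lactate 1.5.
- Fall: 160 − 115 = 45 mmHg, so the patient is eligible.
- MAP: 70 + (115 − 70)/3 = 85 mmHg. SI: 80/115 = 0.70.
- No other entry item is met, and all four HDS items are.

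Meeting HDS also implies the guided arm's no-action branch, since MAP ≥ 70 implies MAP ≥ 65.

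**Dilution of the proportion endpoint.** Let p be the share entering on the fall alone, equal in expectation across arms, and r the HDS rate among the rest. The observed rate is p + (1 − p)r, so the difference is (1 − p)(r₁ − r₀). With an assumed 50% versus 65% among unstable patients:

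| p | Control | Guided | Difference |
|---|---|---|---|
| 0 | 50.0% | 65.0% | 15.0 points |
| 5% | 52.5% | 66.75% | 14.25 points |
| 10% | 55.0% | 68.5% | 13.5 points |
| 20% | 60.0% | 72.0% | 12.0 points |

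**Effect on power.** With an assumed 50% versus 70% and 94 per arm, power is 80.4% at p = 0, 77.0% at 5%, 73.3% at 10% and 65.4% at 20%. Restricting the analysis recovers part of the loss. At p = 10%, 94 × 0.90 ≈ 85 per arm remain, and 50% versus 70% then has 76.3% power against 73.3% unrestricted.

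**Time to HDS.** The same patients add ties at zero in both arms. The size of that effect was not computed.

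**The case against.** The strongest reply is that section 9.2 leaves the binary and time-to-event analyses of secondary endpoints to a later plan. That plan could decide who is at risk at time zero, and the wording of the endpoints (recovery, reaching) leaves room to restrict them. The protocol nowhere says in so many words that patients already stable score zero or count as successes; this follows from the definition and the absence of a baseline rule. That reply stands for the analysis method. It does not remove the mismatch, because the entry rule and the endpoint definition are both fixed in this protocol.

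Other objections limit the point:
- A reader might infer that the criterion cannot be scored at all. The triage condition fixes the current reading and does not bar comparison with a known usual SBP. What is missing is the name of the comparator.
- A reader might infer a large loss. Nothing in the protocol indicates that p is 20% or more. At 5%, the assumed 15 points falls by only 0.75.
- A reader might infer that enrollers could pick a convenient earlier pressure knowing the arm. Section 8.2 has the arm communicated once the patient has arrived and been included, and the consent procedure (11.2.1) puts recruitment before randomisation. Bias between arms is not shown.
- The no-action branch is not peculiar to this route. It has no lactate condition, so a patient admitted on lactate alone can also fall into it, and both arms receive the first bolus.
- Section 2 lists no HDS objective, and the two endpoints are unpowered secondaries among many.

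**Conclusion.** The mismatch is real and follows from the text alone: entry on the SBP fall alone means HDS is already met at triage. The proportion endpoint loses a fraction p of its true difference, and the time endpoint gains uninformative ties. The figures rest on assumed HDS rates, on p being the same in both arms, and on such patients being counted as the definition implies. Because p is unknown, the loss may be small: about 3 points of power at p = 5% under the assumed 50% versus 70%.

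The documents do not support reading this as a flaw in the primary endpoint's sample size, as an unusable criterion, or as demonstrated selection bias. It should be corrected because two endpoints are defined for patients who may have nothing to recover from, and the correction is cheap.

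**What to change.** 1. In section 8.1.2, define both HDS endpoints for patients who do not meet HDS at the triage reading already used for eligibility, with those values recorded before the arm is disclosed and before study treatment. This keeps the comparison randomised. The last reading before randomisation would be a less secure anchor, because section 8.2 lets the randomisation process begin before arrival.
2. Report by arm the number already in HDS at triage, and give a sensitivity analysis in all randomised patients.
3. In section 4.2, name the reference SBP for the fall, and record its value and source in REDCap.
4. Reconcile the entry criterion with the HDS definition. Whether to keep the criterion is for the sponsor, since dropping it changes the population.

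The cost is some wording in two sections, added REDCap entries for the reference SBP, and slightly fewer patients in the two HDS analyses (about 85 instead of 94 per arm if p were 10%). The primary endpoint and the 170/188 do not change.
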